### Statistical methods

Statistical analysis of the primary and secondary endpoints will be conducted in either R or SAS using generalized linear mixed models (GLMMs), which allow for incorporation of correlations due to repeated measures, cluster effects, and potential time effects.

#### Variable selection

Variables such as age, sex, occupation, duration on ART, presence of a treatment buddy, and last viral load will be included based on their relevance to the study objectives and previous literature. The primary outcome will be the change in patient activation measure (PAM) at 6 and 9 months. Changes in PAM score will be analyzed with respect to intervention and control groups, stratified by age category (15–19 vs. 20–24), sex (male vs. female), and duration on ART (<12 months vs. >12 months).

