### Justification for the stepped wedge design

The stepped wedge design was chosen to mitigate contamination bias. In a facility-based setting, randomizing individuals to control or intervention groups within the same facility would result in unintentional exposure of the control group to the intervention. The staggered implementation across clusters also enables continuous refinement of the myCareHub platform based on feedback from earlier clusters, thus improving the intervention over time.

A minimum sample of 480 AYP will be recruited into 16 clusters using a stepwise design, with three-month intervals between successive steps (Table 2).

**Table 2 pdig.0000380.t002:** Study design—cluster randomized trial utilizing a stepped wedge design with 16 clusters and 3 sequences.

CLUSTERS (11–16)	CONTROL	T0.: Baseline survey: Demographics, clinical enquiry, baseline PAM, adherence, VLS, social engagement scores on SSQ6, cluster level retention, cluster VLS.	CONTROL	T1 survey: 3 Mo PAM, adherence, VLS, portal measures: TB ICF, PHQ-9, CRAFFT, SGBV screening, Contraceptive use intention. Feedback on portal, cluster level retention, cluster VLS.	CONTROL	T2 survey: 3, 6 Mo PAM, adherence, VLS, retention, portal measures: TB ICF, PHQ-9, CRAFFT, SGBV screening, Contraceptive use intention. Feedback on portal, cluster level retention, cluster VLS.	INTERVENTION	T3 survey: 3, 6, 9 Mo PAM, adherence, VLS, retention, portal measures: TB ICF, PHQ-9, CRAFFT, SGBV screening, Contraceptive use intention, feedback on portal, cluster level retention, cluster VLS.	INTERVENTION	T4 survey: 6,9 & 12 Mo PAM, adherence, VLS, MAUQ, acceptability score, portal measures: TB ICF, PHQ-9, CRAFFT, SGBV screening, Contraceptive use intention, feedback on portal, cluster level retention, cluster VLS.
CLUSTERS (6–10)					INTERVENTION					
CLUSTERS (1–5)			INTERVENTION							
**TIME**	**TO**	**2 weeks**	**T1** **Mo 1–3**	**2 weeks**	**T2** **Mo 4–6**	**2 weeks**	**T3** **Mo 7–9**	**2 weeks**	**T4** **Mo 10–12**	**2 weeks**

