### Outcome measures

Outcome parameters will be measured at the individual level at pre-specified time points: baseline, every 3 months, and end-line (Table 5). These measurements will be captured using digitized case report forms (CRFs) to ensure accuracy and consistency in data collection.

**Table 5 pdig.0000380.t005:** Summary of outcome variables and analysis measures.

Variable	Definition	Units	Source	Measurement Level	Measurement Period	Comparison Groups	Analysis
PAM	Patient activation measure	100-point scale	PAM-13	Individual	Baseline, 3, 6 and 9 months	Intervention versus Control	Mean change in PAM
Self-reported medication adherence	Estimate of adherence on 0–100% scale	Proportion	Visual analogue scale and adherence questionnaire	Individual	Baseline, 3, 6 and 9 months	Intervention versus Control	% adherence
Viral load suppression (VLS)	Proportion with viral load below detection limit	Proportion	Electronic medical record	Individual	Baseline, 3, 6 and 9 months	Intervention versus Control	% VLS
Cluster retention	Active in care at the end of reporting period/active at the beginning of the period*100	Proportion	Program data	Cluster	Baseline, 3, 6 and 9 months	Intervention versus Control	% retention
Cluster VLS	Percent viral load suppression within cluster	Proportion	Program data	Cluster	Baseline, 3, 6 and 9 months	Intervention versus Control	% VLS
Mobile health application usability score	Numerical score	Mean score	mHealth App Usability Questionnaire (MAUQ)	Individual	End-point	Intervention	Mean scores
Mobile health service acceptability score	Likert-like scale and text	Sub-section scores	Custom acceptability tool	Individual	End-point	Intervention	Mean scores
Social support	Six questions on social supporters	Number of supporters and ratings of support	Social support questionnaire-6 item (SSQ-6)	Individual	Baseline	Intervention	Baseline SSQ-6 scores
Tuberculosis (TB) intensified case finding tool (ICF)	4 questions each scoring 0 or 1	0–4	Portal TB ICF tool, Paper-based TB ICF tool, Program reports	Individual	Continuous	Intervention versus Usual care	% cases diagnosed
							Median time to TB diagnosis
Screening for depression	9 questions each scored 0–3 for total possible score of 27	0–27	Portal patient health questionnaire (PHQ-9)	Individual	Continuous	Intervention versus Usual care	% cases diagnosed

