#### Handling of potential confounding variables and assumptions

Confounding variables identified through exploratory analyses, such as sociodemographic factors and baseline clinical characteristics, will be included in the model to adjust for their effects on PAM scores. Model diagnostics will be performed to ensure appropriate model fit, including checks for residuals and potential overdispersion. Random effects will account for individual variations and cluster effects. The assumptions of GLMMs, including the normality of random effects and the appropriate link function, will be tested using diagnostic plots and statistical tests.

Sensitivity analyses, including the use of causal inference methods, will be conducted to assess the effect of differential patient and cluster characteristics over time, and attrition on the comparison between intervention periods. These analyses will also evaluate the robustness of findings, including the handling of missing data, such as treating PAM scores of 0 and 100 as missing values.

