**Fig 5 pdig.0000380.g005:**
[figure not shown]
Sample size estimation for stepped wedge design.

It is worth noting that the power to demonstrate a difference will be affected substantially by the cluster by time effect. Hemming et al. provided minimal guidance–but did mention a range on that correlation between 0.3 (large effect) to 0.9 (small effect). They strongly suggest a sensitivity analysis on these assumptions, which is provided in Fig 5. Focusing on the green lines, in the presence of high intra-participant variability (individual autocorrelation, IAC) but small time by cluster effects (cluster autocorrelation, CAC), approximately 90% power can be attained with 22 participants per cluster. However, if the time by cluster effect is stronger, power to demonstrate 5 points change drops to 80%. A 10% increase in sample size will be added to account for non-participation, requiring a total of 30 participants per cluster. Based on the above assumptions, the total minimum sample size is therefore estimated at 480. The number of participants lost to follow-up will be monitored throughout the study, and mitigation strategies implemented to accommodate any unforeseen impact by additional recruitment of patients. To compute the sample size for each site, a weighting based on the total AYP will be used. The following formula will be used to obtain a sample for each of the study sites.

$$n_{i}=\frac{N_{i}}{N}$$

where *n_i_* = Sample size for site *i, N_i_* = total AYP in site *i and N* = total AYP in all the study sites

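### The primary PAM response is worded as a change with no baseline PAM term, while the mixed model and sample size describe PAM scores; taken as worded, the T0 survey is used slightly inefficiently

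*Protocol article*

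**What the plan says.** Under Variable selection the protocol article states: "The primary outcome will be the change in patient activation measure (PAM) at 6 and 9 months". Table 5 (Outcome measures) lists the analysis as "Mean change in PAM", and Sample size estimation again calls the primary outcome a change in PAM.

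On covariates, Variable selection says: "Variables such as age, sex, occupation, duration on ART, presence of a treatment buddy, and last viral load will be included". T0 PAM is not in that list. The list is open, and the section on confounding adds further variables, "such as sociodemographic factors and baseline clinical characteristics, will be included in the model to adjust for their effects on PAM scores".

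The model is described under Statistical methods as "generalized linear mixed models (GLMMs), which allow for incorporation of correlations due to repeated measures, cluster effects, and potential time effects", and the section on confounding adds: "Random effects will account for individual variations and cluster effects".

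Table 2 shows that T0 PAM is collected while every cluster is under control: "Baseline survey: Demographics, clinical enquiry, baseline PAM, adherence, VLS". Study population says that the same cohort is measured again at each step.

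Sample size estimation assumes an intra-cluster correlation (ICC) of 0.02, an IAC of 0.8 and low time-by-cluster effects. It quotes a range of 0.3 to 0.9 for the cluster autocorrelation (CAC).

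**The concern.** The endpoint wording and the model wording point to different analyses. ICC, IAC and CAC describe correlations among repeated PAM scores, with the pre-intervention survey counted as a control-period observation. A response defined as change from T0 subtracts that survey with a fixed weight of 1 instead of letting the model estimate how much weight it deserves, and removes T0 as a response. Comparisons of PAM level between persons and between clusters then no longer contribute. A participant without a T0 score has no change score at all, but would still contribute to a score model.

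At stake are a somewhat wider confidence interval than the collected data allow, a power statement that belongs to the score analysis, and a choice between two primary responses that the text leaves open.

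**Working it through.** **The plan's own figure.** 27 per cluster plus 10%: 27 × 1.10 = 29.7, rounded to 30 (27 / 0.9 = 30 as well); 30 × 16 = 480. This reproduces. The power of at least 90% cannot be reproduced, because the SD and a single CAC are not given.

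**Inputs from the protocol article.**
- ICC 0.02 and IAC 0.8; CAC range 0.3 to 0.9 (Sample size estimation). I also ran CAC 1.0 as an upper limit.
- 22, 27 and 30 per cluster (same section).
- 16 clusters as 5/5/6 (Table 2) or 6/6/4 (Table 4).
- Surveys T0-T4 (Table 2) or T0-T3 (the baseline, 3, 6 and 9 months of Table 5).

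**Assumptions.** Equal cluster sizes; two-sided alpha 0.05 (the protocol prints 0.05%); IAC 0.4 as a less favourable case.

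**Formulae.** For m persons per cluster, in units of the PAM variance, the cluster-period means have
- variance = ICC + (1 − ICC)/m
- covariance between periods = ICC × CAC + (1 − ICC) × IAC/m

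The variance of the intervention effect comes from generalised least squares with fixed period effects. The score analysis uses all surveys including T0. The change analysis uses the differences Y_t − Y_0 over the same surveys, with their exact covariance. If the score analysis has 90% power, a variance ratio r gives the change analysis a power of Φ((1.96 + 1.2816)/√r − 1.96).

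**Worked case: m = 27, IAC 0.8, 5/5/6, T0-T4.**
- Variance = 0.02 + 0.98/27 = 0.0563.
- CAC 0.9: covariance = 0.018 + 0.784/27 = 0.0470. Effect variance 0.001822 (score) and 0.001852 (change), r = 1.017, power 89.5%.
- CAC 0.3: covariance = 0.006 + 0.784/27 = 0.0350. Effect variance 0.004060 (score) and 0.004252 (change), r = 1.047, power 88.6%.

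**Range over all settings (22-30 per cluster, both allocations, 4 or 5 surveys, CAC 0.3 to 1.0).**

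| IAC | Variance ratio, change / score | 90% power becomes |
|---|---|---|
| 0.8 (protocol) | 1.011-1.085 | 89.7%-87.5% |
| 0.4 (assumed) | 1.043-1.188 | 88.8%-84.5% |

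At CAC 0.9 and IAC 0.8 alone, the ratio is 1.015-1.030 (power about 89.6%-89.1%).

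**Six and nine months only.** With both analyses limited to T0, month 6 and month 9, taken as calendar surveys T2 and T3, the ratios are 1.023-1.088 at IAC 0.8 and 1.082-1.185 at IAC 0.4. The conclusion does not depend on adding the 3-month survey.

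**Absolute power under assumed SDs (m = 27, IAC 0.8, 5/5/6, T0-T4, 5 points).**
- CAC 0.9, SD 20: above 99.9% for both analyses.
- CAC 0.9, SD 25: 99.7% (score) and 99.6% (change).
- CAC 0.3, SD 20: 97.5% and 97.0%.
- CAC 0.3, SD 25: 88.1% and 86.6%.

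**The case against.** **Subtraction of T0 is inferred.** The article never writes that T0 is subtracted, and Sample size estimation also uses the word change for a difference between the two groups. The mixed model, the individual random effects, the reference to effects on PAM scores and the sample size all fit a score analysis. This stands. It makes the point partly one of ambiguity, but the endpoint is still called a change in three places, and those places do not match the power basis.

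**The covariate list is open.** Baseline clinical characteristics may also be added. This stands: one can say only that T0 PAM is not named, not that it is excluded.

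**Stronger readings that the documents do not support.**
- A reader might infer that T0 is thrown away. It is not: a change score uses it, with a fixed weight.
- A reader might infer that the trial falls below 90% power. The article says at least 90% and gives no SD. For most SDs of 15 to 25, both analyses exceed 90% at the stated IAC.
- A reader might take "in the presence of high intra-participant variability (individual autocorrelation, IAC" as evidence for a low IAC. That sentence gives about 90% power with 22 per cluster, fewer than the 27 required at IAC 0.8. With SD and CAC unchanged, a lower IAC would require more participants. It is weak support, and IAC 0.4 remains an assumption.

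**The change is not wholly without cost.** Modelling every survey adds 3-month exposure to an outcome set at 6 and 9 months, and the note to Table 2 treats six months as the duration needed to assess activation. This stands and is addressed in the fix.

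**Conclusion.** The point holds as a small, inexpensive improvement and a needed clarification. The primary response is named as a change, T0 PAM is not a named covariate, and the model and sample size describe scores. If change from T0 is analysed as worded, the loss at the protocol's own IAC is about 1-9% of variance, or at most 2.5 power points from a 90% starting point. It reaches 4-19% only under an assumed IAC of 0.4. The score model was never less precise over the same surveys in any setting examined. These figures rest on equal cluster sizes, the assumed correlation structure and no missing T0 scores. They do not show that the trial is underpowered.

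**What to change.** State that the primary mixed model takes the PAM score as the response, with T0 included as a control-period observation, fixed period effects, and the cluster and individual random effects already planned. State that the effect is the intervention-control difference in PAM points. If change from T0 is kept as the response, add T0 PAM as a covariate so that its weight is estimated.

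State also which surveys enter the primary effect. If the 3-month survey is included, a single averaged effect could be diluted should activation build over time, so pre-specify the effect at six or more months of exposure as a sensitivity analysis.

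The cost is a few sentences of analysis wording. No new data, visits or participants are needed, and the target remains a 5-point difference on the PAM scale.

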#### Interaction terms

Interaction terms will be included to explore potential interactions between key variables, such as age and sex, or duration on ART and the intervention group. These interactions help to understand whether the effect of the intervention varies across different subgroups.

#### Handling of potential confounding variables and assumptions

Confounding variables identified through exploratory analyses, such as sociodemographic factors and baseline clinical characteristics, will be included in the model to adjust for their effects on PAM scores. Model diagnostics will be performed to ensure appropriate model fit, including checks for residuals and potential overdispersion. Random effects will account for individual variations and cluster effects. The assumptions of GLMMs, including the normality of random effects and the appropriate link function, will be tested using diagnostic plots and statistical tests.

Sensitivity analyses, including the use of causal inference methods, will be conducted to assess the effect of differential patient and cluster characteristics over time, and attrition on the comparison between intervention periods. These analyses will also evaluate the robustness of findings, including the handling of missing data, such as treating PAM scores of 0 and 100 as missing values.

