#### Statistical analysis of secondary objectives

*Self-reported medication adherence*. Self-reported adherence scores, collected at baseline, 3, 6, and 9 months, will be analyzed using GLMMs. These models will account for correlations between repeated measures across the different time points and clustering effects within facilities. The percentage of adherence in the intervention versus control groups will be compared, with adjustments made for potential confounders such as age, sex, and ART duration.

*Viral load suppression*. The proportion of patients achieving viral load suppression (VLS) at baseline, 3, 6, and 9 months will be modeled using logistic regression, adjusted for cluster effects. A comparison between the intervention and control groups will be made, considering time effects and covariates. The percentage of participants in each group who achieve viral suppression will be reported, and changes over time will be assessed.

*Social engagement*. Social engagement scores (SES) from the SSQ6 will be compared across time points (baseline, 3, 6, 9 months) using mixed-effects models. Participation in online communities will be tracked and compared to baseline scores to assess whether the intervention effectively improves social engagement. Differences in social engagement over time will be explored, with subgroup analyses based on age, sex, and baseline social support.

*Portal use and engagement metrics*. The frequency of portal logins, time spent on the portal, and functionalities accessed will be analyzed using descriptive statistics. Regression models will be used to explore relationships between portal use and adherence, activation, and viral suppression outcomes. Portal use will be summarized as engagement metrics (e.g., total logins, average time spent) and correlated with clinical outcomes, including adherence and viral suppression.

*Usability and acceptability scores*. Usability scores from the MAUQ and the custom-designed acceptability survey will be analyzed using descriptive statistics and compared across subgroups (age, sex, ART duration). Generalized linear models will be used to explore the association between usability scores and primary or secondary outcomes. Usability and acceptability will be assessed and reported, with particular attention to how these factors influence engagement with the platform.

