#### Sample size estimation

The primary outcome will be a change in patient activation measure (PAM) [11]. Lin and co-authors found an average effect size of 0.33 in a meta-analysis on studies involving patients with chronic disease reporting change in PAM [19]. Also, a difference of 4 points on the PAM scale is considered clinically important and Marshal et al were able to demonstrate that a 5-point difference was significantly associated with higher odds of CD4 count>200, retention, and viral load suppression [20,21]. Following the definitions as outlined in Hooper et al., 2016 [22], assuming an intra- cluster correlation of 0.02 and individual autocorrelation of 0.8, and only low “time by cluster” effects impacting the PAM scores, the study will require a minimum sample size of 27 per cluster to demonstrate a change of 5 point (green lines in Fig 5) in the activation score between the two groups, assuming the same standard deviation as in Marshall et al, 2013 [21] with a power of at least 90% at an alpha of 0.05% [23].

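### The random effects named for the primary model (participant and cluster) leave out the cluster-by-period component on which the sample size rests; fitted as written, the nominal 5% test of PAM would run at about 8–10% near the design's base case

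*Protocol article*

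**What the plan says.** **Analysis.** Statistical methods places the primary and secondary endpoints under generalized linear mixed models, "which allow for incorporation of correlations due to repeated measures, cluster effects, and potential time effects". The one sentence that lists random effects, under Handling of potential confounding variables and assumptions, reads: "Random effects will account for individual variations and cluster effects". Nowhere is a random cluster-by-period term named, and nowhere is one ruled out.

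**Design.** Sample size estimation follows a closed-cohort stepped wedge parameterisation with an intra-"cluster correlation of 0.02 and individual autocorrelation of 0.8" and low cluster-by-time effects. On that basis "the study will require a minimum sample size of 27 per cluster", inflated to 30. The text after Fig 5 adds that "the power to demonstrate a difference will be affected substantially by the cluster by time effect" and cites guidance in which the corresponding correlation runs from 0.3 (large effect) to 0.9 (small effect).

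**Secondary outcomes.** Adherence is modelled with "clustering effects within facilities", although the randomised units are groups of facilities (Study population; Table 4). Viral load suppression "will be modeled using logistic regression, adjusted for cluster effects", with no participant effect mentioned for its repeated measurements.

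**The concern.** In a stepped wedge trial the intervention contrast changes at the level of the cluster-period. If clusters drift differently from one period to the next, that drift adds directly to the error of the intervention estimate, and recruiting more participants in a cluster does not average it away. A model with only cluster and participant intercepts treats any two periods in a cluster as sharing the whole cluster effect, which means CAC = 1. The design section assumes less than that. The analysis would then report a standard error that leaves out a source of variation the sponsor itself calls influential. At stake are intervals for the primary outcome that are too narrow and an inflated chance of a false positive finding for the portal.

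**Working it through.** **The plan's own figures.** 27 × 1.10 = 29.7, rounded up to 30; 16 × 30 = 480. Both reproduce. The 27 for 90% power cannot be checked, because the SD is taken from a cited study and not printed, and Fig 5 is not shown. The Type I error below does not depend on the SD.

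**Inputs.**
- ICC ρ = 0.02 and IAC = 0.8 (Sample size estimation); CAC from 0.3 to 0.9 (text after Fig 5). The base-case CAC is given only in words; 0.9 is taken as the nearest cited value.
- 16 clusters and five surveys T0–T4 of the same cohort (Table 2). Sequences of 5/5/6 (Table 2) or 6/6/4 (Table 4) give the same results.
- Cluster sizes: either 30 each, or 480 shared in proportion to the Table 4 AYP totals (sum 2,356), which gives 7 to 75 per cluster.
- Assumption: alpha is 5% two-sided. The text prints 0.05%.

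**Variance components** (total variance 1): cluster ρ·CAC; cluster-period ρ(1−CAC); participant (1−ρ)·IAC; residual (1−ρ)(1−IAC).

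**Method.** Fixed period effects. The treatment effect is estimated by generalized least squares with a working covariance that lacks the cluster-period term. Let r be the ratio of its true (sandwich) variance to the variance the model reports. Then Type I error = 2[1 − Φ(1.96/√r)].

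**Hand check, m = 30, IAC 0.8, CAC 0.9.** Residual = 0.98 × 0.2 = 0.196; cluster-period = 0.02 × 0.1 = 0.002. The true period-to-period variance of a cluster mean is 0.196/30 + 0.002 = 0.00853. The model credits (0.196 + 0.002)/30 = 0.00660. So r ≈ 0.00853/0.00660 = 1.29, and the error is 2[1 − Φ(1.96/1.136)] ≈ 8.4%. At CAC 0.3 the cluster-period variance is 0.014, so r ≈ (0.00653 + 0.014)/(0.210/30) = 2.93. The full calculation gives 2.90, an error of 25.0%.

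**Full calculation.** In each cell, the first figure lets the omitted variance fall into the residual and the second lets it fall into the cluster intercept.

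| | CAC 1 | CAC 0.9 | CAC 0.7 | CAC 0.3 |
|---|---|---|---|---|
| 16 × 30, IAC 0.8 | 5% | 8.4 / 8.6% | 15.0 / 15.6% | 25.0 / 26.7% |
| Table 4 proportions, IAC 0.8 | 5% | 9.7 / 9.9% | 18.3 / 19.0% | 30.2 / 31.9% |
| 16 × 30, IAC 0.5 | 5% | 6.3 / 6.4% | 9.0 / 9.2% | 14.0 / 14.6% |
| Table 4 proportions, IAC 0.5 | 5% | 6.8 / 6.9% | 10.5 / 10.7% | 17.2 / 17.8% |

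At CAC 0.95 with IAC 0.8 and equal clusters the error is 6.7%. Unequal sizes do worse because drift dominates in large clusters: at m = 75 and CAC 0.9, the residual part is 0.196/75 = 0.0026, against 0.002 of drift. With Table 4 proportions the reported standard error is about 84% of the true one at CAC 0.9 and about 51% at CAC 0.3 (second convention).

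**Simulation check** (REML-estimated components, 1,500 replicates, Monte Carlo error about 0.6–1.1 points), without the term:
- equal clusters, IAC 0.8: 8.3–9.0% at CAC 0.9 and 26.0% at CAC 0.3;
- Table 4 proportions, IAC 0.8: 10.7% at CAC 0.9. CAC 0.3 was not simulated, so that figure is analytic only;
- equal clusters, IAC 0.5: 6.7% at CAC 0.9.

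With the random cluster-by-period term added (equal clusters, IAC 0.8), the error is 6.3% at CAC 0.9 and 6.1% at CAC 0.3 using z, or 5.6% and 5.5% using t with 80 − 16 − 5 = 59 degrees of freedom.

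**The case against.** The strongest reply is that the sentence on random effects is brief, does not say that only these terms will be fitted, and sits in an article whose SAP is not shown. Statistical methods mentions correlation from possible time effects, and the authors plainly know of the cluster-by-time component, since they ran a sensitivity analysis on it. A list of variance components is often left to the SAP.

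Part of this stands. A reader might infer that the plan deliberately excludes the term; the documents do not show that. But the article does name its random effects, and those named do not match the design section. The time-effects phrase could equally mean fixed period effects, so it does not settle the matter.

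The size also needs care. A reader might infer that 9–10% is the least inflation possible, or that about 30% applies across the cited range. Neither holds: the error is 5% at CAC 1, about 7% at CAC 0.95 and 6–7% at CAC 0.9 with IAC 0.5. Some 30% arises only at CAC 0.3 with unequal clusters. The 0.3–0.9 range is general guidance the protocol cites, not its expectation for this trial.

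The secondary-outcome points are weaker. It is tempting to put the viral suppression standard error at about 1.8 times that of a model with a participant effect. That figure is a linear-scale approximation which borrows the IAC assumed for PAM, and Statistical methods already promises models for repeated measures. The reference to facilities may be loose wording, because Study population defines a cluster as a group of facilities.

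**Conclusion.** The concern holds in conditional form. The named random effects do not include the component on which the sample size depends, and no other passage clearly provides it. If the model is fitted as written under ICC 0.02 and IAC 0.8, the nominal 5% test of the PAM effect has a Type I error of about 8–10% at CAC 0.9 and about 25–32% at CAC 0.3; at CAC 0.9 and IAC 0.5 it is 6–7%. Near the protocol's own base case, the false positive rate is therefore somewhat under double the nominal level. This rests on five survey waves, fixed period effects, a two-sided 5% test, and CAC 0.9 standing for low cluster-by-time effects. The secondary models should be aligned for consistency; no reliable size can be put on their error from the documents.

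**What to change.** State in the protocol or SAP that the primary model has:
- categorical fixed period effects and the intervention indicator;
- random effects for the randomised cluster (16), cluster-by-period, and participant;
- a small-sample degrees-of-freedom correction.

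Use the same structure for the secondary outcomes: the randomised cluster rather than the facility for adherence, and a participant effect for repeated viral suppression (logit link).

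The cost is a few lines of text and one more variance component. At CAC 0.9, intervals widen by about √1.29 = 1.14 (equal clusters) to √1.40 = 1.18 (Table 4 proportions) relative to the model as written, plus a little for the t reference. The power calculation already assumes a CAC below 1.

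As a lesser improvement, for which no effect was computed, adjust for the size stratum used in the randomisation, and use the covariates named under Variable selection in the primary model rather than confounders found by exploratory analysis.
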